### Safety evaluation and adverse events

2.9

Continuous safety monitoring will be conducted throughout the intervention and follow-up periods. All adverse events, including but not limited to skin burns, blisters, local pruritus, cutaneous infections, dizziness, and allergic reactions, will be systematically observed and documented at each treatment and assessment visit. These events will be categorized into three severity levels: mild, moderate, and severe. Mild adverse events primarily consist of minor local itching and mild erythema that do not require clinical intervention. Moderate events are characterized by noticeable blisters, local infections, persistent dizziness, or allergic symptoms that necessitate symptomatic management. Severe events include significant skin burns, syncope, and other life-threatening conditions that require immediate medical intervention. Comprehensive details, including the onset time, clinical features, severity classification, and management strategies, will be meticulously recorded in the case report forms. The causal relationship between adverse events and moxibustion will be rigorously assessed. Qualified professionals will provide timely symptomatic treatment when adverse events occur. All severe adverse events will be promptly reported to the principal investigator and the institutional review board (IRB).

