#### Experimental group: Jianqiao ancient moxibustion treatment

2.7.1

Materials and equipment: Jianqiao ancient moxibustion specially formulated large moxa sticks (23 cm in length, 7 cm in diameter, and 500 g in weight), lighters, 75% alcohol cotton balls, and a specialized Jianqiao ancient moxibustion special moxibustion device. This device comprises a stainless steel three-hole box. Two horizontal rear holes are designed for moxa stick placement, and a vertical top hole connects to an exhaust fan and an external pipe to discharge smoke. The device is mounted on a height-adjustable stainless-steel bracket (Figure 3).Administering practitioner: Licensed acupuncturists with a minimum of 3 years of clinical experience will conduct Jianqiao ancient moxibustion. Prior to study initiation, all practitioners will undergo standardized training and successfully pass an assessment. To ensure intervention consistency, a unified protocol will be rigorously enforced.Preoperative precautions: The ambient temperature of the treatment room will be maintained at 26 °C. Moxibustion treatment will be postponed for patients who are fasting, have recently overeaten, or are experiencing acute exhaustion until they have sufficiently recovered.Operating procedures: ① Position selection: Patients will initially assume a sitting posture with their backs facing the device to expose the lumbodorsal treatment areas. After lumbar and dorsal moxibustion, patients will reposition themselves to face the device, exposing the abdominal treatment areas. ② Moxibustion area selection: The targeted areas include the Guanyuan area (bilateral 7-cm-diameter circular areas on the abdomen covering CV4), the spleen–stomach area (bilateral 7-cm-diameter circular areas on the back covering ipsilateral BL20 and BL21), the kidney area (bilateral 7-cm-diameter circular areas on the lumbodorsum covering ipsilateral BL23), and the baliao area (bilateral 7-cm-diameter circular areas at the lumbosacrum covering ipsilateral BL31, BL32, BL33, and BL34). The schematic diagram of the moxibustion areas is shown in Figure 4. ③ Disinfection: The treatment areas will be routinely exposed and disinfected three times with 75% alcohol cotton balls. ④ Moxa stick ignition: The specially formulated large moxa sticks will be ignited and inserted into the two horizontal holes of the device. The exhaust fan will be activated, and the device will be positioned 15 cm away from the patient’s body surface. ⑤ Moxibustion operation: Suspended moxibustion will be performed sequentially on the kidney area, spleen–stomach area, and baliao area. Each dorsal site will receive 15 min of moxibustion until the local skin becomes flushed. Patients will then turn to face the device and receive another 15 min of moxibustion on the Guanyuan area until local skin flushing occurs. ⑥ Postoperative handling: The device will be removed after moxibustion is completed. Patients will be advised to keep warm and rest adequately.Treatment frequency: Each of the four targeted acupoint areas will undergo moxibustion for 15 min, culminating in a total session duration of 60 min. The treatment protocol consists of three sessions per week for 4 consecutive weeks, resulting in a total of 12 sessions.

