#### Control group: moxa box moxibustion treatment

2.7.2

Materials and equipment: Standard pure moxa sticks (10 cm in length, 1.5 cm in diameter, and 20 g in weight), lighters, 75% alcohol cotton balls, and wooden dual-hole moxa boxes.Administering practitioner: Licensed acupuncturists with a minimum of three years of clinical experience will administer the moxa box moxibustion. Prior to study initiation, all practitioners will undergo standardized training and successfully pass a competency assessment. To ensure intervention consistency, a unified protocol will be rigorously enforced.Preoperative precautions: The ambient temperature will be maintained at 26 °C. Moxibustion should be postponed for patients who are fasting, have overeaten, or are experiencing severe fatigue until they have sufficiently recovered physically.Operating procedures: ① Position selection: Patients will adopt a prone posture to expose the lumbodorsal treatment areas. After back moxibustion, they will switch to a supine position to expose the abdominal treatment areas. ② Moxibustion area selection: The Guanyuan area (bilateral 1.5-cm-diameter circular areas on the abdomen covering CV4), the spleen–stomach area (bilateral 1.5-cm-diameter circular areas on the back covering ipsilateral BL20 and BL21), the kidney area (bilateral 1.5-cm-diameter circular areas on the lumbodorsum covering ipsilateral BL23), the baliao area (two 1.5-cm-diameter circular areas per side at the lumbosacrum covering ipsilateral BL31, BL32, BL33 and BL34). ③ Disinfection: The treatment areas will be exposed and disinfected three times with 75% alcohol cotton balls. ④ Moxa stick ignition: Two moxa sticks will be ignited and inserted into the box holes, after which the box will be placed right above the targeted acupoints. ⑤ Moxibustion operation: Moxibustion will be applied sequentially to the kidney area, the spleen–stomach area, and the baliao area in a prone posture. Each area will be treated for 15 min until the local skin reddens and a mild warm sensation is felt. Patients will then turn supine and receive another 15-min moxibustion on the Guanyuan area following the same standard. Participants’ reactions will be closely monitored, and gauze will be placed under the box to relieve excessive heat stimulation if needed. ⑥ Postoperative handling: Following the session, the moxa box will be removed upon completion of treatment. Remaining moxa sticks and ashes will be properly disposed of, and patients will be advised to keep warm and rest adequately.Treatment frequency: Each of the four targeted acupoint areas will undergo moxibustion for 15 min, culminating in a total session duration of 60 min. The treatment protocol consists of three sessions per week for 4 consecutive weeks, resulting in a total of 12 sessions.

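### Mild erythema is graded as an adverse event although skin reddening is the intended response in every treated area of both arms, so the mild-erythema count and any overall adverse-event rate cannot be read as harm

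*Protocol article*

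**What the plan says.** Section 2.9 of the protocol article defines the lowest severity tier: "Mild adverse events primarily consist of minor local itching and mild erythema that do not require clinical intervention". The same section requires that all adverse events "will be systematically observed and documented at each treatment and assessment visit".

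Section 2.7 describes the skin response at which each application aims:

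- Experimental arm, three dorsal areas (2.7.1): "Each dorsal site will receive 15 min of moxibustion until the local skin becomes flushed".
- Experimental arm, abdomen (2.7.1): participants "receive another 15 min of moxibustion on the Guanyuan area until local skin flushing occurs".
- Control arm, three dorsal areas (2.7.2): "Each area will be treated for 15 min until the local skin reddens and a mild warm sensation is felt".
- Control arm, abdomen (2.7.2): participants "receive another 15-min moxibustion on the Guanyuan area following the same standard".

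Both arms have four areas per session and 12 sessions. The target circles differ in size: for the abdomen, for example, "bilateral 7-cm-diameter circular areas on the abdomen covering CV4" in the experimental arm against "bilateral 1.5-cm-diameter circular areas on the abdomen covering CV4" in the control arm.

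Section 2.9 places blisters, infection, persistent dizziness and allergic symptoms in the moderate tier, and significant burns and syncope in the severe tier. Section 2.8 does not list safety among the outcomes. Section 2.12 names no adverse-event analysis; only its general rule for categorical variables (chi-square or Fisher's exact test) could apply.

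**The concern.** Mild redness that needs no treatment is what section 2.7 sets out to produce, and it is also one of the two signs that section 2.9 names as the main content of the mild tier. No duration, intensity, extent or time of assessment tells the two apart. Staff who follow both sections must log an adverse event when a session has gone as planned. Staff who find that unreasonable must decide for themselves which redness to log.

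At stake is whether the mild-erythema count, and any proportion of participants with at least one adverse event, says anything about harm. The experimental heat source is far larger (500 g sticks against 20 g), so local skin tolerability is an obvious question for this trial. Section 2.10 also sends adverse-event updates to the ethics committee, so the ambiguity affects oversight as well as the final report.

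**Working it through.** The document gives no adverse-event rate, so there is no stated figure to reproduce. The sample size in 2.11 does not bear on the point. Rates marked as assumed below are illustrations only.

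**1. Recording as written.** Four areas × 12 sessions (2.7.1, 2.7.2) = 48 intended reddening responses per participant who completes treatment, spread over 12 visits at which events are documented. One recorded flush is enough to make a participant a case, so the proportion with any event tends to 100% in both arms.

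**2. Recording only now and then.** Let q be the assumed probability that the intended flush is logged at a session, independent between sessions. The proportion with at least one mild event is 1 − (1 − q)^12.

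| q (assumed) | Participants with at least one mild event |
|---|---|
| 0.05 | 46% |
| 0.10 | 72% |
| 0.20 | 93% |

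**3. Masking.** Let h be the proportion with some other harm and e the proportion with erythema recorded, taken as independent. Then any-event rate = 1 − (1 − h)(1 − e). With h assumed at 5% and 15% and e equal in both arms, the difference is 10 points × (1 − e).

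| e (assumed, both arms) | Any-event rates | Difference |
|---|---|---|
| 0% | 5% vs 15% | 10 points |
| 50% | 52.5% vs 57.5% | 5 points |
| 80% | 81% vs 83% | 2 points |
| 100% | 100% vs 100% | 0 |

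**4. Selective recording.** With h assumed at 10% in both arms and e at 30% in one and 60% in the other:

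- 1 − 0.90 × 0.70 = 37%
- 1 − 0.90 × 0.40 = 64%

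The 27-point difference owes nothing to the other harms. Which arm would be the higher is not determined by the document.

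**5. Nominal treated area.**

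- Experimental: 2 circles in each of 4 areas = 8 circles; π × 3.5² = 38.5 cm² each; 307.9 cm² in total.
- Control: 2 circles in each of 3 areas plus 4 in the baliao area = 10 circles; π × 0.75² = 1.77 cm² each; 17.7 cm² in total.
- Ratio: 307.9 / 17.7 = 17.4.

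These are target circles, not observed redness. They show only that the visibility of redness could plausibly differ between arms.

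**The case against.** A reader might infer that the whole adverse-event comparison measures treatment delivery and treated area instead of harm. The document does not support that, for four reasons.

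- The moderate and severe tiers, and itching within the mild tier, do not depend on the intended flush. They include the harms most relevant to a larger heat source and remain interpretable.
- No between-arm adverse-event comparison is stated, so the problem concerns what is collected and how any summary of it would read.
- An area effect is inferred. If every flush is logged, both arms sit near 100% and area cannot show. Only selective recording could bring it in, and its size and direction are unknown.
- Section 2.6 makes clear that practitioners are not blinded, but section 2.9 does not say who records or classifies events. Unblinded classification is possible, not established.

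It can also be said that erythema is absent from the list of example events in 2.9 and appears only in the severity description, so that it may mean the mildest grade of an unwanted reaction. Onset time, clinical features and causality are recorded, and finer instructions may exist in the full protocol or a form guide. This is a single department with standardized training and forms, so divergence between sites is not an issue.

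That reading is sensible, but the text does not state it. The event list is expressly open-ended. Causality assessment cannot separate the two, since the intended flush is by its nature caused by moxibustion. Onset and features help only if a rule says how to use them. And this is more than a detail left out: the article gives a definition, and that definition collides with its own intervention text.

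**Conclusion.** The point holds in limited form. Sections 2.7 and 2.9 give the same sign two roles, intended response and adverse event, with nothing to separate them. The mild-erythema count and any overall adverse-event rate are therefore not interpretable as harm. Recorded literally, both approach 100% in both arms and could hide a real difference; recorded selectively, they depend on unstated judgement, with bias of unknown direction.

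The textual conflict needs no assumption. The sizes do: the 46% to 93% range, the fall from 10 points to 2, and the spurious 27 points all rest on assumed rates and independence, because the document supplies no rates. The 17-fold area ratio follows from the stated diameters but does not measure bias.

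The primary outcome, the sample size and the efficacy analysis are untouched. The inconsistency is confined to the lowest safety tier and to any total that includes it, and it is worth correcting because the correction is cheap.

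**What to change.** Reconcile 2.7 and 2.9. State in 2.9 that the intended transient flushing of 2.7 is an expected treatment response and is not counted as an adverse event, and that erythema counts only when it exceeds that response. The investigators should fix the rule for exceeding it in advance, make it identical in both arms and write it into the case report form. The document supports no particular threshold, so none is suggested here. Report adverse events by arm and by severity tier on that definition. If a fuller protocol or form guide already holds such a rule, bring 2.9 into line with it.

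The cost is about one sentence in 2.9 and one form instruction. This is a recording rule only and leaves the interventions as they are. The downside is that short-lived redness is no longer tabulated as an event.

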### Data management and quality control

2.10

Participant data will be systematically recorded using standardized case report forms. To maintain confidentiality, participants will be anonymized with unique numerical codes, and all research data will be securely stored in an encrypted electronic database. The institutional ethics committee will provide continuous oversight of protocol implementation, the protection of participant rights, and the reporting of adverse events throughout the trial. Researchers involved in moxibustion procedures, scale evaluations, and infrared thermal imaging detection will undergo comprehensive standardized training prior to their participation in the study. Rigorous quality control measures will be applied to participant enrollment, randomization, intervention implementation, and outcome assessment, in strict adherence to the trial protocol. To minimize assessment bias, outcome assessors and statisticians will remain blinded to group allocations. Regular follow-up reminders will be scheduled to enhance participant compliance, and any instances of dropout, loss to follow-up, or protocol violations will be thoroughly documented. Regular verification of source data will be conducted, and updates on trial progress and adverse events will be promptly communicated to the ethics committee.

### Sample size calculation

2.11

Sample size was determined by a previously published randomized controlled trial examining the effects of Governor moxibustion on patients with spleen–kidney yang deficiency pattern CFS, utilizing the FS-14 as the primary outcome measure (29). In that study, the post-treatment FS-14 scores were reported as 4.86 ± 1.43 for the moxibustion group and 6.23 ± 2.73 for the control group. The resulting Cohen’s d was 0.63, signifying a moderate effect size. To achieve a two-tailed significance level (*α*) of 0.05 and a statistical power of 0.80, the required sample size is determined to be 40 participants per group. Accounting for an anticipated 10% dropout rate, a total of 45 participants will be recruited per group, resulting in an overall sample size of 90 patients.

### Statistical analysis

2.12

To mitigate subjective bias, all statistical analyses will be conducted independently by two blinded statisticians utilizing SPSS version 22.0. These statisticians will remain uninformed of group allocations and intervention specifics. The intention-to-treat (ITT) analysis set will include all randomized participants who complete the baseline assessment and receive at least one intervention session, and this set will be used for the primary efficacy analysis. The per-protocol (PP) analysis set will include subjects with good treatment adherence, no significant protocol deviations, and complete outcome data and will be utilized for sensitivity analysis to assess the robustness of the research findings. Data collected at multiple time points will be analyzed using a mixed-effects model for repeated measures, including group, time, and their interaction effects, to evaluate inter-group and temporal differences. Missing data will primarily be addressed through multiple imputation, supplemented by the last observation carried forward method for sensitivity analysis, to minimize bias resulting from data attrition. Covariates such as age, sex, disease duration, and baseline FS-14 scores will be adjusted for in the model to correct for confounding bias due to baseline imbalances. The Bonferroni correction will be employed to adjust for multiple comparisons, thereby controlling for the inflation of Type I error rates associated with simultaneous evaluations of multiple secondary outcomes. Treatment adherence will be quantified as the ratio of sessions actually completed to the total number of sessions planned; statistical comparisons of adherence between groups will be conducted, supplemented by additional sensitivity analyses stratified by adherence status. Continuous data exhibiting normal distribution will be analyzed using the *t*-test, whereas data not conforming to a normal distribution will be assessed via non-parametric rank-sum tests. Categorical variables will be compared using the chi-square test or Fisher’s exact test, as appropriate. All statistical tests will be two-tailed, with a significance threshold set at *a p*-value of < 0.05.

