### Trial design

2.1

This study is a single-center, single-blind, randomized controlled superiority trial. A total of 90 eligible participants diagnosed with CFS with a spleen–kidney yang deficiency pattern will be enrolled. Participants will be randomly assigned in a 1:1 ratio to receive either Jianqiao ancient moxibustion or moxa box moxibustion. The study will span 16 weeks, comprising a 4-week treatment period and a subsequent 12-week follow-up phase.

The trial is registered with the Chinese Clinical Trial Registry (ChiCTR2300079165). The trial flowchart is illustrated in Figure 1, and a detailed timeline is provided in Table 2.

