#### Elimination criteria

2.4.4

Mis-enrolled participants who do not meet the inclusion criteria.Participants with incomplete data or those who commit serious protocol violations that compromise the efficacy assessment.Participants demonstrating poor compliance, those who voluntarily withdraw, or those who utilize unauthorized alternative or prohibited treatments during the trial.Trial termination due to severe adverse reactions or complications.

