### Randomization

2.5

This study will employ simple randomization to group participants. A third-party statistician will utilize SPSS version 22.0 to generate the randomization sequence, ensuring that researchers remain blinded to it. The random numbers are securely sealed in sequentially numbered opaque envelopes and stored in a double-locked cabinet. Upon completion of the baseline assessment and receipt of written informed consent, the envelopes will be opened sequentially in the order of enrollment to reveal group allocation. The allocation sequence will be maintained in strict confidentiality to prevent prediction of subsequent participants’ assignments.

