### Blinding

2.6

Due to the obvious differences in moxibustion devices and procedures, blinding of participants and practitioners is infeasible. To mitigate bias associated with awareness of treatment allocation, outcome evaluators and data statisticians will remain blinded throughout the trial. In addition to patient-reported outcomes, infrared thermal imaging will be utilized as an objective secondary outcome measure to minimize subjective assessment bias. Unblinding will be permitted solely in the event of severe adverse events or upon the completion of data analysis.

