#### Primary outcome

2.8.1

The primary outcome measure will be the Fatigue Scale-14 (FS-14). The FS-14 is a validated 14-item questionnaire for evaluating physical and mental fatigue. Each item utilizes a dichotomous yes-or-no response format and is scored as 0 or 1, with a total score ranging from 0 to 14. Higher scores will indicate more severe chronic fatigue (21, 22). FS-14 assessments will be performed at baseline, week 4 (post-intervention), and week 16 (follow-up).

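### The set named intention-to-treat drops randomised patients who never start treatment, although patients and practitioners know the arm before session 1, so it is a modified ITT set; the size of any bias is unknown

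*Protocol article*

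**What the plan says.** Section 2.12 (Statistical analysis) defines the main set: "The intention-to-treat (ITT) analysis set will include all randomized participants who complete the baseline assessment and receive at least one intervention session". It adds that "this set will be used for the primary efficacy analysis". The only other set is per-protocol, which is narrower: it requires good adherence, no significant deviations and complete outcome data. No analysis of all randomised patients is described. Missing data are to be handled by multiple imputation, with last observation carried forward as a sensitivity analysis. The model adjusts for age, sex, disease duration and baseline FS-14.

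Section 2.5 (Randomization) fixes the order of events: "Upon completion of the baseline assessment and receipt of written informed consent, the envelopes will be opened sequentially in the order of enrollment". Section 2.6 (Blinding) says that "blinding of participants and practitioners is infeasible"; outcome evaluators and statisticians are blinded.

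Section 2.4.4 (Elimination criteria) also lists "Participants demonstrating poor compliance, those who voluntarily withdraw, or those who utilize unauthorized alternative or prohibited treatments during the trial" and does not say whether these criteria apply to the ITT set or only to the per-protocol set.

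**The concern.** ITT protects the comparison because membership of the analysis set is settled by randomisation alone. Here it is settled partly by something that happens afterwards. A rule requiring at least one treatment is usually defended on the ground that the decision to start cannot be influenced by knowing the arm. That defence is not available here, because those who decide whether session 1 takes place are the patient and the practitioner, and both know the allocation.

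If starting depends on the arm and also on prognosis, the remaining groups are no longer those that were randomised, and a reader who sees the label ITT would not know it. Blinded evaluators do not prevent this. The loss occurs before any outcome is assessed, and the primary outcome is a yes/no questionnaire on the patient's own fatigue.

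**Working it through.** **Which condition excludes anyone.** Two conditions are added to being randomised. Completed baseline: under section 2.5 this precedes opening of the envelope, so it should remove nobody after allocation. At least one session: this applies after the arm is revealed, so it is the working filter.

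**Planning figures (section 2.11).** FS-14 was 4.86 (SD 1.43) against 6.23 (SD 2.73), a difference of 1.37.
- Pooled SD = sqrt((1.43² + 2.73²)/2) = 2.18.
- d = 1.37/2.18 = 0.63, as stated.
- Two-sided alpha 0.05 and power 0.80 give 40 per group by the normal approximation (41 by the t-test version).
- 40/0.9 = 44.4, rounded up to 45 per group, 90 in all, as stated.

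The sample size is not in dispute.

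**Shift in an arm mean when non-starters are dropped.** Let k of 45 in one arm not start, none in the other, with their mean FS-14 differing by g from the mean of the whole arm. The mean of those left shifts by k·g/(45 − k). With g = 2.18 (1 SD):
- k = 0: 0
- k = 3: 3 × 2.18/42 = 0.156 points; 0.156/1.37 = 11%
- k = 5: 5 × 2.18/40 = 0.273 points; 0.273/1.37 = 20%

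If g is instead measured against those who start, the shift is k·g/45. Two-sided error with no true difference then follows from SE = 2.179 × sqrt(1/45 + 1/(45 − k)):

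| k | g (points) | Shift | Share of 1.37 | Error |
|---|---|---|---|---|
| 1 | 1 | 0.02 | 2% | 0.050 |
| 3 | 2 | 0.13 | 10% | 0.059 |
| 5 | 3 | 0.33 | 24% | 0.108 |

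All values of k and g are assumptions. The calculation uses unadjusted means, whereas the planned model is adjusted for baseline. The direction is open: losing more-fatigued patients from the moxa box arm flatters that arm, and losing them from the Jianqiao arm flatters Jianqiao.

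**Does imputation from baseline repair it?** A simulation used 45 per arm, SD 2.18, non-starters in one arm only and 1 SD from the arm mean, an assumed baseline–outcome correlation of 0.5, analysis of covariance and 10 imputations. Where baseline does not explain the non-starters' difference:

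| k | Full data | One-session set | All randomised, non-starters imputed |
|---|---|---|---|
| 3 | −0.15 | 0.004 | 0.004 |
| 5 | −0.27 | 0.008 | 0.006 |

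Imputation reproduces the answer of the restricted set. Where baseline fully explains the difference, all three estimates lie within 0.01 of zero. So baseline adjustment either already handles the problem, or imputation from the same variables leaves it in place.

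**The case against.** The strongest reply concerns size. Section 2.11 allows 10% dropout for the whole trial, which is 4.5 of 45 per arm. Three to five losses before session 1 would use 67% to 111% of that allowance in one arm, with none in the other. Nothing in the article supports such numbers. Both arms receive active moxibustion with the same 60-minute sessions, 12 in all, so there is no untreated arm to refuse. Section 2.10 promises that dropout will be documented and section 2.12 compares adherence between arms, so an imbalance need not go unseen. All of this stands. It limits the likely size but does not bring excluded patients back, and the article does not say that non-starters enter the adherence comparison.

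A reader might infer that patients allocated to the conventional moxa box will leave in disappointment and that the primary result will therefore be biased. The document does not support this: it reports no patient preference and no expected number of non-starters. Differential refusal is possible but not shown.

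A reader might also call the trial open-label. Section 2.1 says "This study is a single-center, single-blind, randomized controlled superiority trial", and evaluators and statisticians are blinded. The point needs only that patients and practitioners are not.

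Finally, the objection that imputing non-starters from baseline covariates adds almost nothing is correct, and it determines what the remedy must contain.

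**Conclusion.** The point holds as one of definition and avoidable exposure to bias. The primary set is a modified ITT set under the name ITT, its exclusion rule operates after allocation is known to those who decide on starting, and no all-randomised analysis is described. This is a rule that the article states, so it cannot be put down to detail left for a fuller document.

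The size is unknown. It is near zero if non-starting is rare or similar in both arms. It reaches about 0.16 to 0.27 FS-14 points (11% to 20% of 1.37) only in the assumed high case of 3 to 5 one-sided non-starters, 1 SD from their arm's mean. It would be tempting to read those percentages as the expected bias, or as bias in favour of Jianqiao moxibustion; the document supports neither.

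**What to change.** In section 2.12:
- Define the primary ITT set as all randomised participants, analysed in the arm assigned.
- Invite non-starters to the week 4 and week 16 FS-14 assessments already in the schedule, and use their observed scores.
- Use multiple imputation only for scores still missing, with a missing-not-at-random sensitivity analysis such as a delta adjustment.
- Keep the one-session set as a sensitivity analysis, named modified ITT.
- Report the number of non-starters by arm.
- State that the elimination criteria of section 2.4.4 do not remove patients from the ITT set.

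The cost is a few sentences, some follow-up effort for a few patients, a few imputed records and possibly a slightly diluted effect estimate. The sample size stays at 90, because the 45 per group already carry the 10% dropout allowance. For any non-starter whose assessment dates have already passed, the scores cannot be recovered, and the missing-not-at-random analysis has to carry that uncertainty.
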